## 9. STATISTICS (BIOMETRIC PLAN)

The biometric plan describes the statistical analysis as it is foreseen when the trial is being planned. If circumstances should arise during the trial rendering this analysis inappropriate, or if in the meantime improved methods of analysis should come to light, different analyses may be performed. Any deviations from the biometric plan, reasons for such deviations and all alternative or additional statistical analyses that may be performed, will be described and explained in the detailed Statistical Analysis Plan (SAP) that will be prepared prior to unblinding, as well as in the clinical trial report. The trial statistician in collaboration with the principal investigators (or designees) and ARCHIVEL FARMA, S.L. will be responsible for the preparation of the SAP. Complete procedures regarding the statistical analysis of all variables, the handling of missing values, the determination of trial populations and other details, including the interim analyses, will be detailed in the SAP. The SAP will be finalized before database lock and the clinical trial will be analyzed according to the SAP after database lock.

The creation of tables and listings and the statistical analyses will be performed using SAS® version 9.1 or higher (8).

### 9.1 Data Management

An integrated and validated data management system with remote data entry capabilities and access restrictions will be used for the informatization of the trial data. The MACRO® (12) software has been used for a number of pharmaceutical industries and academic research organizations and it is compliant with Good Clinical Practice (GCP) (13), general recommendations on data management (14), and with regulatory requirements for validation (15, 16). The data will be entered by the local trial investigators using individual login accesses and the system will check for the data consistency and range checks; automatic queries will be raised to be solved by the trial investigators until the database will be considered clean. Data changes due to query forms raised by the monitoring will be also included into the database and identified in the system audit logs. All filters, consistency rules and range checks will be applied according to a data validation plan. Any system access and data changes will be tracked (including old and new values, date-time, user and justification). The data will be available for the monitoring review and for auditing and inspection procedures.

## 9.2 Immunogenicity Data Handling

Immunogenicity data generated will be transferred directly to the trial database and appropriate verifications of the data transfer will be performed to ensure the validity of this process. Once all data has been incorporated into the database, a Blind Data Review (BDR) meeting will be held in order to check the quality of the data and to determine the different trial analysis populations. After the BDR meeting and determination of the trial analysis populations, the database will be locked and the final data will be transferred to the trial statistician.

For the interim analysis partial closures of the database with partially validated data will be prepared with an appropriate log and tracking of the process.

## 9.3 Statistical Methods

### 9.3.1 Safety/Tolerability Parameters

Adverse events will be listed and summarized by system organ class and preferred terms for each treatment group using descriptive statistics.

Tolerability assessments will be listed per patient and summarized using frequency counts or descriptive statistics, as appropriate.

Physical examination results will be summarized using frequency counts and shift tables.

Vital signs, laboratory parameters and ECG parameters will be listed (both absolute and change from baseline results) and summarized per treatment group and visit, for absolute and change from baseline results, using descriptive statistics.

Clinical history results, TST and QuantiFeron, chest X-ray, chest CT scan, CD4 counts, and viral load test results will be listed.

Concomitant medication will be coded using the World Health Organization Drug Reference List (WHO-DRL) and Anatomic Therapeutic Chemical (ATC) classification, listed per patient and summarized per treatment group.

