| Methodology:                          | This is a safety and tolerability trial (Phase II) where three doses will be tested in order to assess their tolerability as a first end-point and will end after three months from the beginning of the assay.                                                                                                                                                                                                                                                                                |

Subjects will be included randomly in different treatment groups as figured below:

| Phase II | n  | LTBI/HIV-                         | n  | LTBI/HIV+                         |
|----------|----|-----------------------------------|----|-----------------------------------|
|          | 12 | RUTI ® (5µg of FCMTb)  | 12 | RUTI ® (5µg of FCMTb)  |
|          | 12 | RUTI ® (25µg of FCMTb) | 12 | RUTI ® (25µg of FCMTb) |
|          | 12 | RUTI ® (50µg of FCMTb) | 12 | RUTI ® (50µg of FCMTb) |
|          | 12 | placebo                           | 12 | placebo                           |

**Tolerability Evaluation:** Toxicity will be evaluated for the subjects visiting the site according to the flow chart; physical examinations (including vital signs measurement) will be performed, as well as local inoculation inspection, and laboratory sampling for safety testing. Chest computed tomography will also be performed in order to detect any Koch reaction at hilar lymph nodes. Adverse events will be recorded after questioning the subjects at each visit, as communicated spontaneously by the subjects, or as observed by the investigators or their collaborators.

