**Statistical Analysis:**

Adverse events will be listed and summarized by system organ class and preferred terms for each treatment group using descriptive statistics. Tolerability assessments will be listed per patient and summarized using frequency counts or descriptive statistics, as appropriate. Physical examination results will be summarized using frequency counts and shift tables. Concomitant medication will be coded using the World Health Organization Drug Reference List (WHO-DRL) and Anatomic Therapeutic Chemical (ATC) classification, listed per patient and summarized per treatment group.

Vital signs, laboratory parameters and ECG parameters will be listed (both absolute and change from baseline results) and summarized per treatment group and visit, for absolute and change from baseline results, using descriptive statistics.

Clinical history results, TST and QuantiFeron, chest X-ray, chest CT scan, CD4 counts, and viral load results will be listed.

The immunogenicity parameters [IFN- $\gamma$  Spot Forming Units in peripheral blood mononuclear cells (PBMCs), IFN- $\gamma$  concentration in whole blood and antibody concentration in sera] will be listed per patient and summarized using descriptive statistics by treatment group and visit. The difference between treatments effect will be studied by comparing the measurement of the immunogenicity parameters. An analysis of covariance (ANCOVA) will be used, with treatment as main effect and the baseline value as covariate. The data and comparisons between the treatments will be described by the least square means adjusted in accordance to the ANCOVA analysis

**Anticipated Trial  
Schedule:**

First subject's first visit: by end of June 2010

Last subject's last visit: November 2010

Preliminary results: February 2011

Draft report: March 2011

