### OBJECTIVES:

- To evaluate the safety and tolerability of three different doses (5, 25 and 50 µg of FCMtb) of one formulation of the novel antituberculous vaccine RUTI® in subjects with LTBI compared to placebo.
- To evaluate the immunogenicity of three different doses (5, 25 and 50 µg of FCMtb) of one formulation of the novel antituberculous vaccine RUTI® in subjects with LTBI compared to placebo.

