### 3. TRIAL DESIGN

#### 3.1 Endpoints to be Measured During the Trial

Primary endpoint: Safety and tolerability

- Adverse events
- Vital signs, including blood pressure, pulse, respiratory rate, body temperature
- Physical examinations
- Laboratory tests (standard haematology, serum biochemistry and urinalysis; and CD4 counts and viral load in HIV+ patients)

Secondary endpoint: Cellular immunogenicity response

- Immunogenicity by measuring the number of IFN- $\gamma$  spot-forming units among PBMCs stimulated with five antigens using a non commercial ELISPOT test, after cryopreservation of PBMC from peripheral blood.
- Immunogenicity by measuring the number of IFN- $\gamma$  spot-forming units among PBMCs stimulated with two (ESAT-6 CFP-10) antigens using a commercial ELISPOT test: TIGRA, after cryopreservation of PBMC from peripheral blood.
- Long-term whole blood assay (stimulation of diluted whole blood with PPD for seven days), the “*WHO assay*”.
- Sera will be frozen to be further tested for humoral response against *M. tuberculosis* antigens (antibodies to LAM, 16kDa and 38kDa mycobacterial antigens).

Additional laboratory markers to be determined:

- NAT-2 genotyping: to account for INH metabolism status.
- Retention of cryo-preserved PBMC for retrospective testing.

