#### Tolerability

Local: evaluation of the injection site: The investigator will evaluate the site of injection for redness, pain, swelling, and induration and functional limitation at the time points indicated in the events schedule (~~Figure 18~~~~Figure 18~~).

Redness, swelling and induration will be evaluated and recorded on the CRF as: 0 = absent, 1 = mild, 2 = moderate, 3 = severe. If present, the extent of the reaction will be measured in mm. Pain will be recorded, after questioning the subjects, by means of a Visual Analogue Scale (VAS from 0 to 100). The presence of abscess, ulceration or necrosis will also be evaluated, measured and adequately documented.

Focal: evaluation of the hilar lymph nodes for inflammation: An un-contrasted thoracic computerised tomographic scan will be performed prior to first vaccine inoculation and four weeks after the last one (2nd vaccine inoculation) to evaluate the change in size of the hilar lymph nodes.

Systemic: body temperature  $\geq 38^{\circ}\text{C}$ , asthenia, sweating, malaise, headache, dizziness, nausea, myalgia, arthralgia, rash and generalised pruritus will be reported.

Adverse events will be reported by the subject for the duration of the trial both spontaneously and after questioning.

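### Chest CT, CD4 count and viral load are planned as listings, although the protocol treats them as primary safety or tolerability measures and summarises their neighbours by treatment group

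*Protocol*

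**What the plan says.** The safety objective in Section 2 is to evaluate three doses "in subjects with LTBI compared to placebo". Section 3.1 opens its endpoint list with "Primary endpoint: Safety and tolerability", and one item under it reads "Laboratory tests (standard haematology, serum biochemistry and urinalysis; and CD4 counts and viral load in HIV+ patients".

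Chest CT is not in that list, but the protocol gives it a tolerability purpose. The synopsis, under tolerability evaluation, says "Chest computed tomography will also be performed in order to detect any Koch reaction at hilar lymph nodes". Section 7.1, under Tolerability (focal), plans one scan before the first inoculation and one four weeks after the second, "to evaluate the change in size of the hilar lymph nodes".

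For the analysis, Section 9.3.1 says "Clinical history results, TST and QuantiFeron, chest X-ray, chest CT scan, CD4 counts, and viral load test results will be listed", and the statistical paragraph of the synopsis says "Clinical history results, TST and QuantiFeron, chest X-ray, chest CT scan, CD4 counts, and viral load results will be listed". Other sentences in Section 9.3.1 go further. Tolerability assessments are listed and also summarised. Vital signs, laboratory and ECG parameters are listed and also summarised by treatment group and visit, both as levels and as change from baseline.

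**The concern.** One sentence puts three measures collected before and after vaccination together with clinical history, TST, QuantiFeron and chest X-ray, which are obtained at pre-screening or screening. A listing suits the second kind, because there is no post-vaccination value to compare. It does not suit the first.

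A line listing lets a reader find an extreme individual. It does not show whether CD4 count, viral load or node size moved on average in one arm relative to another. All subjects take isoniazid for a month before the first inoculation, so change during the vaccination period is best read against the placebo arm. If the sentence is followed as written, the report would hold these data but give no summary by arm of level or change.

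**Working it through.** **1. The protocol's own figures.** The protocol states no number for these three measures. Section 9.6 says there was no formal sample size calculation. Its Table 8 concerns the chance of seeing adverse events among 72 vaccinated subjects and does not bear on this point. The check is therefore mainly a comparison of sections.

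**2. Role, timing and planned analysis side by side.**

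| Measure | Role | Collected (Figure 19) | Specific sentence, 9.3.1 and synopsis | General sentence, 9.3.1 |
|---|---|---|---|---|
| CD4 count, viral load (HIV+) | Laboratory tests within the primary endpoint (3.1) | Screening, Days 28, 35, 63, 84 | Listed | Laboratory parameters: listed and summarised by group and visit, with change |
| Chest CT | Focal tolerability (7.1); not in the 3.1 list | Days 28, 84 | Listed | Tolerability assessments: listed and summarised |
| Clinical history, TST, QuantiFeron, chest X-ray | Screening | Pre-screen or screening | Listed | None |

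The first inoculation follows the Day 28 assessments and the second is on Day 56. CD4 and viral load therefore have one pre-vaccination value at Day 28 and three later values. CT has one before and one after. The specific and general sentences give different answers for the first two rows and agree only for the third.

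**3. What reaches a table by arm in any case.** Section 7.1 has investigators enter clinically relevant laboratory changes in the adverse event section of the CRF. The definition in Section 7.2.1 counts abnormal diagnostic and laboratory results as adverse events. Section 9.3.1 summarises adverse events by treatment group. A CT finding or a CD4 change judged clinically relevant should thus appear by arm, placebo included. Levels and subclinical change would not.

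**4. Precision of an optional contrast with placebo.** Inputs: 12 subjects per arm in each HIV stratum (Table 4), no dropout, equal SD in the arms. The protocol gives no SD, so results are in SD units.

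95% half-width = t × SD × √(1/n₁ + 1/n₂)

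- CD4 or viral load, one dose vs placebo, 12 vs 12: 2.074 × 0.408 = 0.85 SD
- CD4 or viral load, all doses vs placebo, 36 vs 12: 2.013 × 0.333 = 0.67 SD
- Node size, one dose vs placebo, strata combined, 24 vs 24: 2.013 × 0.289 = 0.58 SD
- Node size, all doses vs placebo, 72 vs 24: 1.986 × 0.236 = 0.47 SD

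Subjects who leave after their first inoculation are not replaced (Section 4.3), so the actual widths would probably be larger.

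**The case against.** The strongest case against has four parts.

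- **The sentence does not say that these data are only listed.** CD4 and viral load are laboratory tests in Section 3.1, and CT is a tolerability assessment in Section 7.1, so the general sentences could cover them. A reader might infer that the protocol expressly excludes the three from summary. The text does not say so. Listing only is the more natural reading, because nearby sentences name both steps and this one names a single step, but it remains an inference. On the generous reading the section still says two things about the same data and needs reconciling.
- **The adverse event tables already compare arms.** A reader might infer that these safety questions get no comparison with placebo at all. Step 3 of the working shows otherwise, and this part of the objection stands. The monitoring committee also sees unblinded results, although that is not a reported final analysis.
- **No safety parameter in Section 9.3.1 gets a between-group difference or an interval.** To require them for these three measures would ask more than the protocol gives adverse events. This stands. The widths above also show that such contrasts could not reliably detect a modest shift.
- **The SAP is to give the full procedures.** It is not at hand, and it could add summaries without breaking the protocol. But Section 9 presents the biometric plan as the foreseen analysis, with deviations and additional analyses to be explained. The protocol has stated an analysis here, so the point is not a detail left open.

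**Conclusion.** The point holds as an inconsistency that should be corrected. The protocol states a listing for measures that it elsewhere treats as part of the primary safety endpoint (CD4 count and viral load) or as a tolerability assessment of change (CT). If that wording is followed, there is no summary by group of level or subclinical change in up to 48 HIV+ subjects for CD4 and viral load, or in up to 96 subjects for hilar node size.

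It would go too far to conclude that the primary endpoint has no result by treatment. Adverse events, vital signs and standard laboratory tests are all summarised by group. CD4 and viral load are part of one item in that endpoint, in half the subjects, and CT is not named in Section 3.1.

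The defect is a missing descriptive summary, not a missing test. The conclusion rests on reading the listing sentence as it stands; the half-widths rest on full follow-up and equal SDs.

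**What to change.** In Section 9.3.1 and in the statistical paragraph of the synopsis, remove chest CT, CD4 count and viral load from the listing sentence. State that they are listed and summarised descriptively by treatment group, like the other safety parameters:

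- CD4 count and log10 viral load in HIV+ subjects: level, and change from Day 28 (pre-vaccination), at Days 35, 63 and 84.
- Hilar node size: change from Day 28 to Day 84, and the number of subjects with enlargement.

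Differences from placebo with 95% confidence intervals may be added for each dose and for all doses combined, labelled as exploratory and imprecise.

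The cost is a few extra tables and no added procedures. One condition applies: Section 7.1 specifies scoring and millimetre measurement on the CRF for injection-site reactions but describes no such record for the nodes. Node size would have to be captured as a measurement from the two scans already planned.

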### 9.3.2 Immunogenicity Parameters

The immunogenicity parameters (IFN- $\gamma$  Spot Forming Units in peripheral blood mononuclear cells (PBMCs), IFN- $\gamma$  concentration in whole blood and antibody concentration in sera) will be listed per patient and summarized using descriptive statistics by treatment group and visit. The difference between treatments effect will be studied by comparing the measurement of the

immunogenicity parameters. An analysis of covariance (ANCOVA) will be used, with treatment as main effect and the baseline value as covariate. The data and comparisons between the treatments will be described by the least square means adjusted in accordance to the ANCOVA analysis.

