This Phase I clinical trial was also the first approach to study the mechanisms of action of the vaccine RUTI® in humans. A wide range of assays were planned, in order to screen any immunological response enhanced by the vaccination as well as to determine which assays should be performed in future clinical trials. The results obtained showed us that a specific immunological response was triggered by the vaccination, which sometimes were significantly different from the one obtained in the placebo-vaccinees, and could also be detected by the commercial ELISPOT and ELISA assays designed to diagnose LTBI. A general overview to the results shows us that there exists a dose-related tendency for most of the assays conducted. Highest doses (especially a dose of 200 µg of FCMtb) showed a maximum of highest results, evidenced in terms of the ELISPOT and ELISA techniques to determine the specific IFN-γ secretion. Even though, a dose of 25 µg of FCMtb achieved a polyanitigenic response, wider than a dose of 100 µg of FCMtb and similar to the one reached by dose of 200 µg of FCMtb, a fact easily recognizable in the ELISPOT assays. Moreover, even if in the ELISA studies (less sensible and specific than ELISPOT) doses of 100 and 200 µg of FCMtb showed the highest results, a dose of 25 µg of FCMtb showed a discrete but clear increase of the IFN-γ secretion attributable to the vaccination. The most important problem of the ELISA results is the high specific results for some of the antigens obtained by the placebo group in latest time points. Those results are meant to be due to some of the individuals that conferred this group. In spite of

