## 1.5 Description of the Population to be Studied

The present trial has been designed to test the safety, tolerability and immunogenicity of a treatment regimen against LTBI consisting of RUTI® vaccination after pre-treatment with INH for one month. HIV infected and non-infected subjects will be enrolled as subjects. As a Phase II trial, all the subjects will be TB latently infected (with a positive tuberculin skin test (TST)+ and a QuantiFeron-TB-Gold positive result). Recruitment will be done prospectively in 96 LTBI HIV negative (n=48) and positive (n=48) subjects, once lack of active TB would be ensured. Including HIV- subjects in this trial will provide essential comparative data about safety and immunogenicity that will allow a better understanding of the HIV+ patients demonstrated responses to the vaccine.

There will be no gender preferences for subjects enrolled into this clinical trial.

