#### 3.2 Description of the Type/Design of Trial to be Conducted (Diagram of Trial Design, Procedures and Stages)

The trial will be a double-blinded, randomized and placebo-controlled to test three doses of RUTI® and will last three months.

Three different RUTI® doses and placebo will be tested, randomizing assigned both in HIV+ and HIV- subjects, as figured in [Table 4](#)~~Table 4~~. Each subject will be randomized to receive one of the four treatments (placebo, 5, 25, 50 µg), after completion of one month INH pre-treatment (one tablet of 300mg/day, p.o.). Each subject will receive two administrations of the same treatment, 28 days apart. Subjects will be monitored until one month after the second inoculation with RUTI®. All trial procedures will be performed according to the schedule displayed in [Figure 17](#)~~Figure 17~~.

[figure not shown]

**Figure 17** Chart summarizing the trial design of both phases of the clinical trial. Subjects will be recruited at the three PAREXEL South Africa sites.

Every subject will receive the Informed Consent, with all the activities and requirements of the trial. After signing it, they will be screened in order to guarantee the compliance of the inclusion and exclusion criteria.

Once included in the trial, the subjects can do their daily activities, always following the principal investigators instructions, and communicating any event that could interfere with the trial's objectives.

The day-to-day management of the clinical trial has been organized in function of the laboratory work and the clinical part to be done. An organisation chart including the decision-making mechanism for safety and immunogenicity is included below, the timing has also been added ([Figure 18](#)~~Figure 18~~).

[figure not shown]

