**Figure 18 Day to day management**

### 3.3 Randomization and Blinding

After all subjects received one-month of INH treatment, a total of 48 HIV+ subjects and 48 HIV- subjects will be randomised to one of four pre-treatment groups (12 subjects in each treatment group) and will receive either placebo, 5, 25 or 50 µg of FCMtb RUTI® as indicated in [Table](#)

~~4Table 4~~ below. Each subject will have two inoculations of the applicable RUTI® dose or placebo, 28 days apart, once the safety is ensured.

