## 9.6 Number of Subjects Planned to be Enrolled (Sample Size)

A total of 96 subjects will be enrolled: 48 HIV negative (HIV-) and 48 HIV positive (HIV+) subjects. The subjects of both phases of the clinical trial will be randomized to one of four treatment groups as presented in [Table 4](#) (Section 3.3).

Sample size is not based on a statistical rationale. Since this is an exploratory safety and tolerability phase II trial, no formal sample size calculations have been made. However, the numbers foreseen in this trial, 12 subjects group, are comparable with the standard sample sizes used in these studies (Table 8).

**Table 8** In the following tables we give the probabilities of detecting an adverse event between 0.1 to 10% and the exact confidence intervals for the whole set exposed to the vaccine (N=32)

| Event rate | N  | Probability to detect at least: |          |          |
|------------|----|---------------------------------|----------|----------|
|            |    | 1 Event                         | 2 Events | 3 Events |
| 0.1%       | 72 | 7.0%                            | 0.2%     | 0.0%     |
| 0.5%       | 72 | 30.3%                           | 5.1%     | 0.6%     |
| 1.0%       | 72 | 51.5%                           | 16.2%    | 3.6%     |
| 2.0%       | 72 | 76.7%                           | 42.3%    | 17.5%    |
| 3.0%       | 72 | 88.8%                           | 64.0%    | 36.7%    |
| 4.0%       | 72 | 94.7%                           | 78.8%    | 55.4%    |
| 5.0%       | 72 | 97.5%                           | 88.1%    | 70.5%    |
| 6.0%       | 72 | 98.8%                           | 93.5%    | 81.4%    |
| 7.0%       | 72 | 99.5%                           | 96.5%    | 88.8%    |
| 8.0%       | 72 | 99.8%                           | 98.2%    | 93.4%    |
| 9.0%       | 72 | 99.9%                           | 99.1%    | 96.3%    |
| 10.0%      | 72 | 99.9%                           | 99.5%    | 97.9%    |

  

| N  | n | %    | 95%CI |       |
|----|---|------|-------|-------|
| 72 | 0 | 0.0% | 0.0%  | 5.1%  |
|    | 1 | 1.4% | 0.2%  | 7.5%  |
|    | 2 | 2.8% | 0.8%  | 9.6%  |
|    | 3 | 4.2% | 1.4%  | 11.5% |
|    | 4 | 5.6% | 2.2%  | 13.4% |
|    | 5 | 6.8% | 3.0%  | 15.1% |

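### Allocation is 12 per arm within each HIV group, but the stated ANCOVA has no HIV term and Section 9.3 specifies no summary by HIV status

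*Protocol*

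**What the plan says.** **Design.** Protocol Section 9.6 states: "A total of 96 subjects will be enrolled: 48 HIV negative (HIV-) and 48 HIV positive (HIV+) subjects". Section 3.3 says that "a total of 48 HIV+ subjects and 48 HIV- subjects will be randomised to one of four pre-treatment groups (12 subjects in each treatment group"). Table 4 shows the eight cells of 12. Section 3.3 also says that stratification is needed, without naming the factor; Table 4 and Section 3.2 point to HIV status.

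**Reason for two HIV groups.** Section 1.5: "Including HIV- subjects in this trial will provide essential comparative data about safety and immunogenicity", to help interpret the responses of the HIV+ subjects.

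**Analysis.** Section 9.3.2 (repeated in the synopsis): "An analysis of covariance (ANCOVA) will be used, with treatment as main effect and the baseline value as covariate". Immunogenicity is summarised by treatment group and visit. Section 9.3.1: "Adverse events will be listed and summarized by system organ class and preferred terms for each treatment group using descriptive statistics". Vital signs, laboratory, ECG and concomitant medication are also summarised per treatment group. Tolerability and physical examination have no stated grouping. CD4 counts and viral load are to be listed only.

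**Meaning of treatment group.** Section 3.2: "Each subject will be randomized to receive one of the four treatments (placebo, 5, 25, 50 µg"). Section 9.6 has subjects "randomized to one of four treatment groups". Both give four groups of 24. The count of 12 per treatment group in Section 3.3 fits only eight HIV-by-dose cells.

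**The concern.** The analysis that the protocol states does not follow the design that it states. A factor that structures allocation, and for whose sake half the subjects are enrolled, is absent from the model and from every summary grouping named in Section 9.3. Two things are at stake.

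- **Precision.** If HIV+ and HIV- subjects differ in IFN-γ or antibody response after baseline adjustment, that difference stays in the residual variance. Standard errors are then larger than the design requires.
- **The comparison itself.** Nothing in Section 9.3 says how the data in the two HIV groups will be set side by side. If this is settled only after unblinding, the comparison becomes post hoc.

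The double use of treatment group adds to this. Under one reading the tables pool HIV+ and HIV-; under the other they are already split.

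**Working it through.** **Inputs from the protocol.** N = 96, four treatments, 12 per treatment in each HIV group, hence 24 per arm overall and 36 vaccinated per HIV group (3 × 12). The protocol gives no SD, effect size, alpha or power for the ANCOVA, so there is no ANCOVA figure to reproduce. The effect sizes, HIV gaps, 5% level and 80% power below are assumptions.

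**1. The plan's own figure.** Table 8 gives the chance of seeing at least one event among the vaccinated. Its rows use N = 72 (its caption says 32). With 1 − (1 − p)^N:
- p = 1%: 1 − 0.99^72 = 51.5%, as stated.
- p = 5%: 1 − 0.95^72 = 97.5%, as stated.

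These figures pool both HIV groups. The same formula gives:

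| Subjects | p = 1% | p = 5% |
|---|---|---|
| 72, pooled | 51.5% | 97.5% |
| 36, one HIV group | 30.4% | 84.2% |
| 12, one cell | 11.4% | 46.0% |

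**2. Residual degrees of freedom** (all 96 subjects with data):
- As written: 96 − 4 treatment means − 1 baseline slope = 91.
- With an HIV main effect: 90.
- With HIV and treatment-by-HIV: 96 − 8 − 1 = 87.

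An ANCOVA with treatment read as eight cells also has 87. The two readings of treatment group are therefore two different models.

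**3. Effect of leaving the stratum out.** Let g be the HIV+/HIV- gap left after baseline adjustment, in within-stratum SDs. A balanced two-level factor adds g²/4 to a residual variance of 1, so the inflation factor is 1 + g²/4. The estimated SE grows by its square root, while the true sampling SE of a contrast balanced over strata does not. The actual two-sided error is 2 × [1 − Φ(1.96 × √(1 + g²/4))]. Power for an assumed 0.8 SD dose-versus-placebo difference (24 versus 24) is Φ(0.8/√(2/24) − 1.96 × √(1 + g²/4)).

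| Assumed g | Variance factor | SE factor | Actual error at nominal 5% | Power |
|---|---|---|---|---|
| 0 (or stratum in model) | 1.000 | 1.000 | 5.0% | 79.1% |
| 0.25 | 1.016 | 1.008 | 4.8% | 78.7% |
| 0.5 | 1.063 | 1.031 | 4.3% | 77.4% |
| 1.0 | 1.250 | 1.118 | 2.8% | 71.9% |

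**4. What HIV-specific estimates can show.** The detectable difference at 80% power, two-sided 5%, is (1.960 + 0.842) × SE, in SD units:
- Pooled, 24 versus 24: 2.802 × √(2/24) = 0.81 SD.
- Within one HIV group, 12 versus 12: 2.802 × √(2/12) = 1.14 SD.
- Dose-versus-placebo by HIV interaction: 2.802 × √(4/12) = 1.62 SD.

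**The case against.** The strongest reply has four parts.

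- **The SAP.** Section 9 describes the plan as what is foreseen, allows other analyses, and leaves complete procedures to an SAP prepared before unblinding. A reader might infer from Section 9.3 that the HIV comparison will never be produced. The documents do not support that: the SAP is not at hand, and per-patient listings could be split by HIV status. What remains is that the protocol states the model terms, without HIV. Section 9 requires deviations from the biometric plan to be explained, so an SAP that adds HIV would have to be justified against this text.
- **The eight-cell reading.** Section 3.3 and the synopsis table allow treatment group to mean an HIV-by-dose cell, so some tables may already be split. This stands for the descriptive summaries. It is weaker for the ANCOVA, because Section 3.2 defines four treatments. A reader might also infer that every safety table pools HIV status. That goes too far: tolerability and physical examination state no grouping, and CD4 and viral load are only listed.
- **The objectives.** Both are dose versus placebo in subjects with latent infection. The HIV comparison is rationale, not an objective, and the trial is exploratory with descriptive primary safety endpoints. This stands: no formal test of HIV differences is owed, and the ANCOVA serves a secondary endpoint.
- **Small loss.** With a small residual gap the cost is slight (1.6% of variance at 0.25 SD). This also stands.

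A reader might further fault the analysis scale or the choice of baseline visit. Section 9.3.2 fixes no scale, and both are ordinary SAP detail, so neither is part of this point.

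**Conclusion.** The point holds as a mismatch between design and stated analysis. Allocation is within HIV group and Section 1.5 relies on the comparison, while Section 9.3 specifies no HIV term and no summary by HIV status, and treatment group has two meanings.

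A reader might infer that the dose-versus-placebo estimates are biased. They are not: with 12 per arm in each HIV group, omitting the stratum costs precision and makes tests conservative. The cost is about 1.6%, 6% or 25% more residual variance for residual HIV gaps of 0.25, 0.5 or 1.0 SD. These gaps are assumptions, since the protocol gives no basis for choosing among them. The calculation also assumes that HIV status is the stratification factor, that the cells stay close to balanced, and normal approximations.

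This should be fixed, but it does not threaten the trial's validity. It is a free improvement.

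**What to change.** - **Section 9.3.2 and the synopsis:** add HIV stratum to the ANCOVA beside treatment and baseline. Add an exploratory treatment-by-HIV term that yields dose-versus-placebo estimates with 95% CIs within HIV+ and within HIV-. Say that these are imprecise: 12 versus 12, with a detectable interaction of about 1.6 SD at 80% power.
- **Sections 9.3.1 and 9.3.2:** present the safety and immunogenicity summaries by dose within HIV status and overall.
- **Sections 3.2, 3.3, 9.3 and 9.6:** use one definition of treatment group throughout, and name HIV status as the stratification factor if that is what is meant.

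The cost is wording, extra table columns and 1 to 4 of 91 residual degrees of freedom. No subjects, visits or samples are added. The change should be made before unblinding.
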